#### Application of the SR during the main trial

The SR product will be replaced by paid study personnel throughout the intervention period. Both participants and study staff will be blinded as to whether the product is active (SR) or is a placebo. Products will be replaced every 4 weeks as recommended by the manufacturer. Study teams will be employed to ensure proper storage of unused products at the site and supply management and coordination for the timely replacement of products. Study teams will also perform periodic, unannounced spot checks in a random 10% of enrolled HHs during intervention on a quarterly basis to monitor SR product compliance (installation according to manufacturer specifications) and ITN usage, if available. Each product will have a unique code, which will be recorded at the time of installation and the time of replacement.

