### Adverse event reporting and harms {22}

The SR product contains transfluthrin, a chemical used in currently available HH mosquito control products such as mosquito coils. Exposure to the product may cause mild eye and skin irritation, however, these effects are typically transient and disappear after time. The product may be harmful if chewed on or swallowed, so HH owners will be advised to keep it away from children. The SR product will be fixed at a position out of the reach of children and will be monitored at replacement to ensure it has not been moved. If a product is found to have been removed from its position in the HH, study staff will discuss with the HH owner to determine why it was removed and if there was any problem that led to its removal. Study staff will also reiterate safety precautions that should be taken in regard to the SR product.

AEs and SAEs of interest will be collected through passive surveillance by CHVs on cohort participants and other HH members receiving the study product. Additionally, AE and SAEs of interest will be solicited from study participants during follow-up visits (every 2 weeks) either in the house or clinic. We will also rely on passive surveillance of the outpatient registers at the local health facilities for reports of AE/SAE. Additionally, we may collect unsolicited reports during compound visits and/or product replacement. Anyone experiencing the SAEs or AEs of interest will be encouraged to seek care at the study clinic where clinical staff will attend to them at no cost.

An AE includes any noxious, pathological, or unintended change in anatomical, physiological, or metabolic functions as indicated by physical signs, symptoms, and/or laboratory detected changes occurring in any phase of the clinical study whether associated with the study intervention or placebo. This definition includes an exacerbation of pre-existing conditions or events, intercurrent illnesses. A SAE is any untoward medical occurrence that results in death, is life-threatening, results in persistent or significant disability/incapacity, requires in-patient hospitalization or prolongation of existing hospitalization, or is a congenital anomaly/birth defect in the offspring of a study subject. In addition, important medical events that may jeopardize the participant or may require intervention to prevent one of the other outcomes listed above will be considered serious.

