All SAEs will be recorded on the appropriate SAE case report form (CRF), followed through resolution by a study physician, and reviewed by a study physician.

Symptomatic uncomplicated or severe malaria infection will be coded as AEs as will any other acute illness, throughout the 24 months of the study. Clinical malaria will be recorded in the same fashion as other AEs. In general, uncomplicated malaria will constitute an AE and severe malaria will constitute an SAE. Anticipated day-to-day fluctuations of pre-existing conditions that do not represent a clinically significant exacerbation need not be considered AEs. Discrete episodes of chronic conditions occurring during a study period will be reported as AEs to assess changes in frequency or severity. Pre-existing conditions or signs and/or symptoms (including any that are not recognized at study entry but are recognized during the study period) present in a participant prior to the start of the study will be recorded on the participant’s CRF.

AEs will be documented in terms of a medical diagnosis. When it is not possible to make a specific medical diagnosis, the AE will be documented in terms of signs and/or symptoms observed by the investigator or reported by the subject at each study visit. Any hospitalization will be considered a SAE.

AEs to be recorded as endpoints will be pre-defined based on SCJ. toxicology reports of “probable,” “possible,” “plausible,” and “unlikely.” “Probable”includes sensory irritation (oral and dermal). “Possible”includes nausea/vomiting (oral), skin irritation/rash (dermal), and runny nose (inhalation). “Plausible” includes salivation, and “unlikely” includes eye irritation and headache.

AEs and SAEs will be recorded throughout the study. SAEs and the study reports will also be provided to Mali’s Faculté de Médecine et d’Odonto Stomatologie - Faculté de Pharmacie (FMOS-FAPH) ethical committee as required by their current Standard Operating Procedures. Study teams will record AEs for every 2-week surveillance period at the time of house visit (during active malaria detection) and for the 30-day surveillance period at the time of clinic visits (during passive malaria detection). SAEs will be recorded at the time of death, hospitalization. Assessment of SAE relatedness to intervention will be conducted by the study clinician in-country with confirmation/verification by the DSMB Medical Monitor based on the study clinician SAE report and trends in other SAE datasets.

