AEs and SAEs will be reported in future publications. Harms will be coded in accordance with MedDRA at time of safety outcome reporting. Summaries of symptom-based AEs, SAEs, and death reports observed during the studies will be reviewed by the trial DSMB at predetermined checks (quarterly). The AE/SAE will be labeled “Probable,” “Possible,” “Plausible,” or “Unlikely” due to SR. Summary statistics of AEs/SAEs, including mean, minimum, and maximum frequencies and percentages across clusters among enrolled subjects, will be provided by the treatment arm. Statistical comparisons of the AE/SAE rates between the two arms will be conducted upon the completion of the study. Two sets of statistical analyses will be run. One set will compare the proportion of having at least one occurrence in each symptom-based AE/SAE during the whole study between the two arms, and the other will compare the total number of occurrences for each AE/SAE between the two study arms. If the data collected permits meaningful statistical hypothesis testing, p-values from the treatment comparisons will be reported, with multiplicity correction via the FDR approach [21].

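### The two final AE/SAE comparisons pool the whole follow-up, so an irritation excess limited to the first weeks after installation would be heavily diluted; add one early-window comparison

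*Protocol article*

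**What the plan says.** Under Adverse event reporting and harms {22}, the protocol defines two sets of formal safety comparisons:

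- The first is an ever/never comparison by arm: "One set will compare the proportion of having at least one occurrence in each symptom-based AE/SAE during the whole study".
- The second is a comparison of counts, described in these terms: "and the other will compare the total number of occurrences for each AE/SAE between the two study arms".

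Timing is fixed as well: "Statistical comparisons of the AE/SAE rates between the two arms will be conducted upon the completion of the study". Any p-values are to be reported "with multiplicity correction via the FDR approach". Neither comparison has a time window, a period term or time since installation. The words about the whole study are attached only to the first. For the second, pooling follows from the use of totals and from testing at completion.

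The same section says of mild eye and skin irritation that "these effects are typically transient and disappear after time". It pre-defines the AEs of interest, among them sensory irritation, skin irritation or rash, runny nose, nausea or vomiting, eye irritation and headache. On recording it states: "Study teams will record AEs for every 2-week surveillance period at the time of house visit". Clinic visits use a 30-day period.

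Under Application of the SR during the main trial, product is replaced every 4 weeks, and "Each product will have a unique code, which will be recorded at the time of installation and the time of replacement".

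**The concern.** A comparison pooled over 24 months suits harm that is steady, late or cumulative. It suits poorly an effect that appears when the product is first hung and then fades. In that case the excess falls in a handful of child-fortnights and is averaged with about 50 fortnights of ordinary background symptoms. The ever/never comparison has a second weakness: for a common symptom most children in both arms will report it at least once in two years, so the proportions approach a ceiling.

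The data for a time-specific look are largely collected already, since the installation is recorded and house visits give 2-week AE records. What is at stake is the tolerability statement that accompanies the findings submitted to the WHO VCAG. The trial could report no difference in irritation when there was a moderate excess in the first weeks.

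**Working it through.** The protocol gives no power, sample size or background rate for the safety comparisons, so there is no stated figure to reproduce. The check is an illustration.

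**Inputs from the protocol**
- 30 clusters × 26 children = 780 per arm; 780 × 0.65 = 507 if 35% are lost (Sample size {14}).
- 24 months with intervention, about 52 two-week periods.
- Product replaced every 4 weeks; DSMB review quarterly.

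**Assumptions, not in the protocol**
- Background risk p0 of 0.25% to 5% per child per 2 weeks.
- Risk multiplied by R (2 or 3) in the first two periods only, no effect afterwards.
- Two-sided 5%. This first calculation ignores clustering, uneven follow-up and the FDR correction.

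**Formulas**
- First 4 weeks: 1 − (1 − p0)² against 1 − (1 − R·p0)².
- Ever in 24 months: 1 − (1 − p0)^52 against 1 − (1 − R·p0)²(1 − p0)^50.
- Ratio of totals: (50 + 2R)/52.
- Power: pooled-variance normal approximation for two proportions; for totals, a Wald test on the log ratio with variance 1/T0 + 1/T1. Only rejections in the direction of harm are counted, so values can fall just below 0.05.

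**Dilution.** R = 2: 54/52 = 1.04. R = 3: 56/52 = 1.08.

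**Worked case: p0 = 1%, R = 3, 780 per arm**
- First 4 weeks: 1.99% v 5.91%, power 0.98.
- Ever in 24 months: 40.7% v 43.1%, power 0.16.
- Totals: T0 = 780 × 52 × 0.01 = 405.6; T1 = 780 × 56 × 0.01 = 436.8. The log ratio is 0.074, its standard error √(1/405.6 + 1/436.8) = 0.069, z = 1.07, power 0.19.
- With 507 per arm the three powers are 0.89, 0.12 and 0.14.

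**Range at 780 per arm**

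| p0 | R | First 4 weeks | Ever | Totals |
|---|---|---|---|---|
| 0.25% | 2 | 0.21 | 0.04 | 0.05 |
| 0.25% | 3 | 0.51 | 0.08 | 0.08 |
| 0.5% | 2 | 0.37 | 0.05 | 0.06 |
| 0.5% | 3 | 0.80 | 0.11 | 0.12 |
| 1% | 2 | 0.63 | 0.07 | 0.08 |
| 1% | 3 | 0.98 | 0.16 | 0.19 |
| 2% | 2 | 0.90 | 0.09 | 0.12 |
| 2% | 3 | 1.00 | 0.21 | 0.33 |
| 5% | 2 | 1.00 | 0.08 | 0.23 |
| 5% | 3 | 1.00 | 0.20 | 0.67 |

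The ceiling shows at p0 = 5%, R = 3: 93.1% v 94.4% ever affected.

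**With clustering and loss.** A simulation used 60 clusters of 26, 35% loss over 24 months, cluster-level t-tests, and assumed background risks of 2–10% per 2 weeks, between-cluster CV 0.2–0.5 and between-child CV 0.5. For a doubling in the first 4 weeks, power was 5–16% for the two planned comparisons and 77–100% for a first-4-week comparison.

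**Where the planned approach copes**
- First-quarter counts (six periods): ratio (4 + 2R)/6 = 1.33 for R = 2 and 1.67 for R = 3. At p0 = 1% and 780 per arm, power is 0.32 and 0.79. In the clustered simulation a first-12-week look had about 29–96% power for the 4-week doubling.
- R = 5 with p0 of 2% or more: the totals have power 0.85–1.00 and ever/never 0.61–0.64.
- An excess recurring after every replacement: totals had 76–100% power in the clustered simulation, depending on the between-cluster CV.

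**The case against.** A reader might infer that the plan predicts an early harm and then makes it invisible. The protocol supports neither half of that.

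- Transient describes how an effect resolves, not when it starts. Fresh product goes up every 4 weeks, so irritation could recur at each replacement, and the totals would then collect it. This stands: the dilution holds only for an excess confined to the period after first installation.
- The DSMB section provides for routine Medical Monitor review and a quarterly comparison of AE and SAE rates by arm. This stands as a partial safeguard. The protocol does not say that the review is split by time since installation or that it will be reported.
- Only eye and skin irritation are called transient. Runny nose, vomiting and headache are not, and eye irritation and headache are elsewhere classed as unlikely. This stands, and it limits the point to irritation-type AEs.
- Every rate and effect size is assumed, and the FDR correction is not modelled. This stands. The correction would lower the power of all the comparisons, including the early one.
- Clinic visits use 30-day recall and no section aligns visits with replacement, so a clean split into first and second fortnight after each replacement is not assured. This stands.
- Ever/never and totals are conventional, and time-split tables may be in the SAP, which is not shown. They are conventional, and nothing here is false or contradictory. But the protocol names exactly two sets of comparisons, and neither uses the timing it collects.

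A reader might also infer that the whole-study ever/never comparison should give way to an early window. It should not: that would drop late and cumulative harm, SAEs included, from that comparison.

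**Conclusion.** The point holds as a cheap improvement. The two final comparisons do not match one plausible time course of the irritation that the protocol describes. If the excess is confined to about the first 4 weeks after first installation, a doubling or tripling shrinks to a whole-follow-up ratio of about 1.04–1.08, and power in both comparisons is mostly under 20%. The exceptions among the assumed settings are mainly the totals for common symptoms, reaching 0.67 at a 5% background with a tripling. A first-4-week comparison does much better throughout, though for rare symptoms it too can be weak (0.21 at a 0.25% background with a doubling).

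The size rests on assumed background rates, effect sizes and duration. If whole study were read to include the 6-month baseline, which the outcome list covers for AEs, dilution would be greater; the harms section itself speaks of 24 months.

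**What to change.** Keep both whole-study comparisons. Add to Adverse event reporting and harms {22}:

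1. For the pre-defined irritation-type AEs, one pre-specified comparison by arm of at least one occurrence in the first 4 weeks after the household's first installation, accounting for cluster and included in the FDR set. State how a 30-day clinic report that straddles installation is assigned.
2. A descriptive table of AE rates by arm and time since first installation, and since replacement where the house-visit records allow it.

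This needs no new data, visits or staff. The cost is a few more safety estimates and a slightly larger FDR family.

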### Frequency and plans for auditing trial conduct {23}

FhiClinical will be responsible for clinical monitoring at the protocol implementation level, ensuring subjects will be properly consented, data will be appropriately gathered, safety events will be documented and reported as required, the investigational product will be managed and distributed per specifications, and study close-out activities will occur on a timely basis.

### Plans for communicating important protocol amendments to relevant parties (e.g., trial participants, ethical committees) {25}

Protocol amendments will be submitted to the Sponsor and local IRBs as well as the WHO Ethical Review Committee (ERC) for approvals. Any amendments, outcomes, analyses, or more will be communicated in person and virtually. Face-to-face meetings will be held between Lead PI, scientific director, site staff, and members of the site-specific countries where the trials are being conducted. These meetings will include National Malaria Control Programs, MOHs, other in-country public health officials, members of civil society, religious leaders, and key beneficiaries. These meetings will be critical as the trials will be in-progress and the topics addressed will be pertinent to facilitating further execution of the trial. Due to the project design and geographic location of the study team, teleconferences will be another method of formal project communication. Stakeholder teleconferences will be scheduled as needed to review and assess study progress and issues. Agendas for all teleconferences will be drafted by UND and distributed.

### Dissemination plans {31a}

Dissemination of results includes submission to WHO/VCAG, workshop with study partners, on-site meetings in Mali, and presentations at scientific meetings and/or peer-reviewed publications.

## Discussion

While the malaria burden has seen substantial reductions since 2000, malaria remains a serious public health concern, particularly in sub-Saharan Africa due to gaps in protection from ITNs and IRS. Supplemental tools such as SRs may address these gaps in coverage to further reduce the malaria burden. The role for SR products in malaria public health vector control are likely to be greatest in settings where early-evening and/or outdoor biting by *Anopheles* mosquitoes are not subject to the effects of ITNs and IRS or in complex emergencies where many people are housed in temporary shelters which are not conducive to ITN or IRS implementation. In addition, the active ingredient in SR products operates through a different mode of action and has demonstrated behavioral effects against both insecticide susceptible and resistant vectors responsible for transmitting multiple human pathogens [6]. Thus, SRs may serve as a tool in areas where insecticide resistance limits the effectiveness of ITNs and IRS and reducing selection pressure for insecticide resistance and thereby maintaining the tools’ natural life span [22].

There are thousands of registered SR products already in the market, adopted, and used for protection from nuisance biting; however, there is presently no public sector that uses SR products for disease control due to insufficient evidence for WHO policy recommendation. Over the past decade, national and international meetings have convened academics, industry, funders, and global public health experts, including WHO representatives, to discuss the role of SR products in the reduction of arthropod-borne diseases based on existing evidence.

A SR vector control product class is currently under WHO assessment for public health value, however, the biggest evidence gap is the lack of epidemiological data needed to demonstrate public health impact across a range of eco-epidemiological settings to inform a potential WHO policy recommendation for the incorporation of SR products into current multi-lateral disease control programs. In 2017, the WHO VCAG recommended additional clinical trials to evaluate SR against malaria in Africa [23]. These knowledge gaps must be addressed to inform WHO SR policy recommendations. This cRCT in Mali will serve as one of the additional trials to generate evidence to support WHO decision-making in regards to a recommendation.

If the WHO VCAG endorses a policy recommendation for the SR class to be recommended for public health use, national disease control programs will have the option to adopt a SR policy and “next-in-kind” SRs (e.g., with active ingredients to include other volatile pyrethroids such as metofluthrin) can be marketed within the public health channel without the need to undergo WHO VCAG assessment, incentivizing SR product research. Outputs will align with those of other global health stakeholders addressing residual malaria transmission, insecticide resistance, as well as access and barriers to market introduction of new vector control products. If the SR product is effective, it can be deployed to complement other vector control interventions such as ITNs to help mitigate the problem of insecticide resistance and times of vector biting where ITNs may be ineffective to further drive malaria towards elimination.

## Trial status

Under protocol version 8.2 from January 24, 2021, recruitment for the baseline cohort began July 8, 2021 and final subject enrolment for the baseline cohort has been completed on July 26, 2021.

The study has currently completed the baseline phase (as of January 15, 2022), whereby participants have been recruited, screened, enrolled, and followed up without intervention for 6 months. Baseline data analyses are ongoing to verify underlying assumptions of malaria incidence, coefficient of variation, and loss to follow-up. Recruitment, screening, and enrolment of subjects for follow-up with intervention are scheduled to be completed in March 2022.

## Abbreviations

AE: Adverse events
AEGIS: Advancing Evidence for the Global Implementation of Spatial Repellents
AI: Active ingredient
AL: Artemether-lumefantrine
CI: Confidence interval
CRC: Center for Research Computing
cRCT: Cluster-randomized control trial
CRS: Catholic Relief Services
CV: Coefficient of variance
DSMB: Data Safety and Monitoring Board
EIR: Entomological inoculation rate
ERC: Ethical Review Committee
HBR: Human biting rate
HH: Household
HIN: Household identification number
HLC: Human landing catch
ICF: Informed consent form
IRS: Indoor residual spraying
ITN: Insecticide treated net
ITT: Intention to treat
LTFU: Loss to follow-up
MOH: Ministry of Health
MRTC: Malaria Research and Training Center
PE: Protective efficacy
PI: Principal Investigator
RDT: Rapid diagnostic test
SAE: Serious adverse event
SCJ: SC Johnson, A Family Company
SR: Spatial repellent
UND: University of Notre Dame
VCAG: Vector Control Advisory Group
WHO: World Health Organization
